## **11.8. Safety Analysis**

Adverse event and clinical laboratory data will be reviewed on an ongoing basis during the study to evaluate the safety of the patients.

### **11.8.1. Extent of Exposure**

A frequency distribution of the number of days of treatment completed by the patients will be produced by treatment group. Total dose received by each subject will be summarised by treatment group. Patients with treatment compliance below 80% or above 120% will be listed.

### **11.8.2. Adverse Events**

The proportion of patients reporting each type of adverse event will be tabulated for each treatment group. Adverse events will be coded and grouped using the MedDRA dictionary. The following summaries of adverse events will be provided:

- all adverse events
- treatment-related adverse events
- adverse events leading to withdrawal from study medication
- serious adverse events.

Full details for all adverse events will be listed.

### **11.8.3. Clinical Laboratory Evaluations**

The readings obtained at Visit 2 (randomisation) of each laboratory test will be used as the baseline value for that test. Laboratory data will be summarised for each parameter at all visits by treatment group. Absolute change from baseline will also be calculated for each subject and summarised by visit and treatment group.

A laboratory value that is on or within the reference range is considered normal. A laboratory value that is outside the testing laboratory's reference range is considered an abnormal laboratory value. A laboratory value that is above the upper limit of the reference range is considered high abnormal. A laboratory value that is below the lower limit of the reference range is considered low abnormal.

The threshold laboratory values are defined in terms of a multiplicative factor of the testing laboratory's reference range or as an absolute value. A threshold value may also be defined as a change of clinical concern from baseline. These will be defined in the Reporting and Analysis Plan (RAP). A laboratory value that is above the threshold is considered a high threshold value. A laboratory value that is below the threshold is considered a low threshold value. The proportion of patients exceeding the threshold criteria for each of these laboratory values at any post-baseline visit will be summarised by treatment group. A subject's post-baseline laboratory value will only be considered to be a threshold if it is more extreme than the baseline result and satisfies the criteria for a threshold value as defined above. A listing of patients with any threshold value during the study will also be produced.

Box plots will be used to display graphically all safety laboratory values. Any outliers will be detailed in a supporting listing.

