### **6. STUDY ASSESSMENTS AND PROCEDURES**

A Time and Events Table is shown in Appendix 1.

Screening procedures should be conducted over a maximum period of 4 weeks prior to Visit 2 (baseline/randomisation).

The visit window for weekly visits is +/- 2 days. Study medication should be taken for 14(+/- 4) days. Visit 5 (day of surgery) must be conducted on the day following the last dose of study medication. Visit 6 must be conducted on the day after surgery, ie. 2 days following the last dose of study medication.

Visit 7 (follow-up) should be conducted 14 days (+/- 3 days) following the last dose of study medication.

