**6.2.4.3. Haematology and Clinical Chemistry**

Blood samples will be taken at each visit EXCEPT 4 and 6 (as indicated in Table 1) for routine haematology and clinical chemistry testing. All samples will be transferred to a central laboratory (Quest Diagnostics) for analyses. Sample handling and shipping instructions will be provided separately.

Parameters to be tested are listed below.

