#### **10.2.1. Surgery-Related Events or Outcomes Not Qualifying as SAEs**

Carotid endarterectomy is associated with significant morbidity/mortality (risk of stroke, bleeding, death). Such post-operative events will not be recorded as SAEs.

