### **10.5. Time Period, Frequency, and Method of Detecting AEs and SAEs**

Any pre-existing conditions or signs and/or symptoms present in a patient prior to the start of the study (i.e. before informed consent) should be recorded in the Medical/Surgical History section within the CRF.

In order to fulfil international reporting obligations, SAEs that are related to study participation (e.g. procedures, invasive tests, change from existing therapy) or are related to a concomitant medication will be collected and recorded from the time the patient consents to participate in the study until he/she is withdrawn or completes.

Any medical occurrences which occur after informed consent is obtained but prior to starting active or randomised treatment will be documented on the Baseline Signs & Symptoms section within the CRF.

All AEs occurring after administration of the first dose of study medication and on or before the final visit must be reported on the Adverse Event form in the CRF. All AEs must be recorded irrespective of whether they are considered drug related.

At each visit/assessment in the period defined above, AEs will be evaluated by the investigator and recorded in the appropriate AE/Serious AE section of the CRF.

Any AEs already documented at a previous assessment and designated as ongoing, should be reviewed at subsequent visits as necessary. If these have resolved, the documentation in the CRF should be completed. If an AE changes in intensity/frequency then this should be recorded as a separate event (i.e. a new record started).

As a consistent method of soliciting AEs, the patient should be asked a non-leading question such as:

"Have you felt different in any way since starting the new treatment/or since the last visit?"

or

"How do you feel?"

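### The laboratory threshold table and the adverse event tables each merge the pre-surgery and post-operative periods into one count per arm, which dilutes any drug-placebo difference

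*Protocol*

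**What the plan says.** Safety and tolerability is a secondary objective (Protocol Section 2.2). The passages that set the counting windows are these.

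- **Laboratory thresholds, Section 11.8.3:** "The proportion of patients exceeding the threshold criteria for each of these laboratory values at any post-baseline visit will be summarised by treatment group".
- **Laboratory draws, Section 6.2.4.3:** "Blood samples will be taken at each visit EXCEPT 4 and 6 (as indicated in Table 1) for routine haematology and clinical chemistry testing". With Visit 2 as baseline, the post-baseline draws are Visits 3, 5 and 7.
- **Adverse events, Section 11.8.2:** "The proportion of patients reporting each type of adverse event will be tabulated for each treatment group". The collection window is in Section 10.5: "All AEs occurring after administration of the first dose of study medication and on or before the final visit must be reported".
- **Timing, Section 6:** "Visit 5 (day of surgery) must be conducted on the day following the last dose of study medication", and "Visit 7 (follow-up) should be conducted 14 days (+/- 3 days) following the last dose of study medication".
- **Surgical risk, Section 10.2.1:** "Carotid endarterectomy is associated with significant morbidity/mortality".

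Other safety outputs are laid out differently. Laboratory values, their changes from baseline, and vital signs are summarised by visit and arm (Sections 11.8.3 and 11.8.4.1). ECGs are recorded only at baseline and Visit 5, and the Visit 5 recording may be made up to 24 hours before surgery (Section 6.2.2).

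**The concern.** The threshold table counts a patient once, whether the limit was crossed at Visit 3 on drug or at Visit 7 after an operation. The AE table counts a patient once per event type over a window with surgery in its middle. In both, an event caused by the operation carries the same weight as one seen on drug before it.

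Because all arms have the operation, it adds a similar background to each of them. That background reduces the difference between arms and, at the rates tried below, widens its standard error. With 33 randomised patients per arm, a drug effect on an event type that surgery also causes often would be harder to see. The counting rule for thresholds is written in the protocol itself; Section 11.8.3 leaves only the threshold values to the Reporting and Analysis Plan (RAP).

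**Working it through.** **The plan's own figure.** The protocol states no design figure for the safety tables. The arm size used here comes from Section 11.4.1: difference ln 2 = 0.693, SD 0.7, two-sided alpha 2.5%, 90% power. The noncentral t calculation gives 27 per group (power 90.5%), as stated. For 20% loss, 27 x 1.2 = 32.4, rounded up to the stated 33; 27/0.8 = 33.75 would give 34. Nothing below turns on that one patient.

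**How much of the window follows treatment.** Dosing lasts 10 to 18 days. Visit 7 is 11 to 17 days after the last dose, hence 10 to 16 days after surgery.

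- Smallest share of the window after the last dose: 11/(18+11) = 38%.
- Largest share: 17/(10+17) = 63%.

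**Drug exposure after surgery.** The half-life is 25 to 45 hours (Section 1.1).

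- Five half-lives: 5 x 25/24 = 5.2 days to 5 x 45/24 = 9.4 days after the last dose.
- Remaining at the nominal Visit 7 (336 h): 0.5^(336/25) = 0.01% to 0.5^(336/45) = 0.6%.

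Visit 7 is therefore essentially off drug, but the first post-operative days are not.

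**Dilution.** Let p0 and p1 be the pre-surgery event rates on placebo and active. Let s be the rate at which surgery alone causes the same event type, equal in all arms and independent of the drug. The pooled rates are

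q = 1 - (1-p)(1-s), so q1 - q0 = (1-s)(p1 - p0),

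with SE = sqrt{[q0(1-q0) + q1(1-q1)]/33}.

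All event rates are assumptions; the protocol gives none. For p0 = 2% and p1 = 15%:

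| s | q0 | q1 | Difference (points) | SE (points) | z | Fisher power, two-sided 5% |
|---|---|---|---|---|---|---|
| 0 (pre-surgery only) | 2.0% | 15.0% | 13.0 | 6.7 | 1.95 | 23.6% |
| 2% | 4.0% | 16.7% | 12.7 | 7.3 | 1.74 | 21.1% |
| 5% | 6.9% | 19.3% | 12.4 | 8.2 | 1.51 | 18.5% |
| 10% | 11.8% | 23.5% | 11.7 | 9.3 | 1.26 | 14.9% |
| 30% | 31.4% | 40.5% | 9.1 | 11.8 | 0.77 | 8.0% |
| 60% | 60.8% | 66.0% | 5.2 | 11.8 | 0.44 | 4.6% |

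For larger assumed effects the direction is the same. With 5% versus 25%, Fisher power is 51% before surgery, and 30%, 20%, 16% and 10% pooled at s = 10%, 20%, 30% and 50%. With 5% versus 35%, it is 84%, then 60%, 45%, 35% and 18%.

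The protocol plans no hypothesis test for safety. Fisher power is used here only as a yardstick for how visible a difference would be.

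**The case against.** **Most safety outputs are not pooled.** A reader might infer that the safety tables as a whole merge the two periods. They do not. Laboratory values and vital signs are by visit, and there is no ECG after Visit 5 to merge. There are separate tables for treatment-related AEs and for AEs leading to withdrawal of study medication; the latter can hardly include post-operative events. All AEs and all patients with a threshold value are listed. This stands and limits the point to two outputs. The by-visit summaries show values and changes, however, and do not split the threshold counts; listings support case review but are not a comparison of arms.

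**Surgery does not hide or bias the effect.** A reader might infer that the operation masks any drug effect. Randomisation balances it across arms, and the formula scales the difference by (1-s) without erasing it. This stands.

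**Pooling is not the main reason an effect could be missed.** In the illustration, detection is only 23.6% with no surgical events at all. For event types that surgery seldom causes, the loss is small: 21.1% at s = 2%. The arm size limits detection more than pooling does. This stands too.

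**Visit 7 is not always post-operative.** Patients who withdraw after randomisation complete an early-withdrawal Visit 7 (Section 9.2.1), and some will not have been operated on. This stands.

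**Post-operative stroke, bleeding and death should not fill the SAE table.** Section 10.2.1 keeps them out of it. Section 10.5 still requires all AEs to be reported, so they may enter the AE tables.

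**The RAP may split AEs by period.** It may: Section 11.8.2 is an outline and does not forbid a split, and the RAP is not shown. This weakens the AE half of the point. The any-visit rule for laboratory thresholds is fixed in the protocol.

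**Conclusion.** The point holds for two outputs: the laboratory threshold proportions in Section 11.8.3 and the AE incidence tables in Section 11.8.2. Each gives one count per arm that merges the pre-surgery and post-operative periods, so surgical events dilute a drug-placebo difference there.

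The size depends on s for each event type. The loss is small at 2% to 5% and substantial at 30% or more, where a 13-point difference falls to 9.1 points or less and z from 1.95 to 0.77 or less. This rests on assumed event rates, on a surgical rate equal in all arms and independent of the drug, and on a drug effect confined to the time before surgery. If the drug altered the post-operative rate, the simple factor would not apply.

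The documents do not support the stronger inference that a false finding of no difference is likely because of pooling. At 33 per arm, low power remains under either layout. Nor do they support calling the pre-surgery table the only valid reading: the pooled table is a legitimate comparison over the whole window, and exposure continues for about 5 to 9 days after the last dose. This is a cheap improvement to a stated counting rule, not a flaw that invalidates the safety analysis.

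**What to change.** Keep the pooled tables and add the following beside them.

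1. **Section 11.8.3:** proportions exceeding each threshold by visit (3, 5 and 7) and arm. Keep early-withdrawal Visit 7 samples from patients not operated on separate from post-operative ones. Class the Visit 5 sample as before or after surgery by its draw time, since the protocol does not say when on that day the safety sample is taken.
2. **Section 11.8.2:** AE incidence for two periods, first dose to start of surgery and start of surgery to Visit 7, assigned by onset.

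Neither period need be named the main display. A split at surgery separates before from after the operation, not on drug from off drug, and the tables should say so.

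The cost is extra tables, each with fewer events, from data largely collected already. AE onset time is needed on the day of surgery, and the draw time for the Visit 5 laboratory sample. No patient procedure need change.

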### **11.8.4. Other Safety Measures**

#### **11.8.4.1. Vital Signs**

For the purpose of reporting, baseline assessments will be defined as the readings obtained at Visit 2, randomisation.

Vital sign data will be summarised for each parameter at all visits by treatment group. Absolute change from baseline will also be calculated for each subject and summarised by visit and treatment group.

All vital signs data will be listed.

#### **11.8.4.2. ECGs**

ECGs will be performed at Visits 2 and 5. The results from these will be classified as normal, abnormal not clinically significant and abnormal clinically significant. These classifications will be summarised by treatment group. ECG results at Visits 2 and 5 will also be classified as no clinically significant change from baseline or clinically significant change from baseline. These classifications will also be summarised by treatment group. Clinically significant ECG findings will be listed and summarised by treatment group.

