### **2.2. Secondary**

- To determine the change in Lp-PLA2 activity in blood after treatment with SB-480848
- To determine the change in Lp-PLA2 mass in blood after treatment with SB-480848
- Lp-PLA2 mass in plaque after treatment with SB-480848, compared with placebo
- To evaluate the dose response effects of SB-480848 on plasma and plaque Lp-PLA2 levels
- Levels of defined biomarkers in plaque after treatment with SB-480848, compared with placebo
- To determine the change in levels of defined biomarkers in blood after treatment with SB-480848
- To investigate the correlation between biomarkers and Lp-PLA2 in blood and plaque after treatment with SB-480848
- To characterise the pharmacokinetics (PK) of repeat oral doses of SB-480848 and its metabolite (SB-553253) in this patient population
- To investigate the pharmacodynamics (PD) of SB-480848 following repeat oral administration to this population
- To further investigate the safety and tolerability of SB-480848 through observations of adverse experiences, vital signs, laboratory tests, and effects on 12-lead ECG.
- To determine a change in the oxidised lipids and their metabolites including lyso-PC levels in plasma and in carotid plaques after 14(+/-) days treatment with SB-480848 compared to placebo.

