**6.2.2. Electrocardiogram (ECG)**

A standard 12-lead ECG will be recorded at Visits 2 (or at visit 1 if it is logistically easier) and 5. At Visit 5 the ECG can be taken up to 24 hours prior to surgery. If possible, the same equipment should be used throughout the study. A clear copy of the trace must be clearly labelled with patient number, protocol number, centre number and date, it must be signed and dated by the investigator and placed in the CRF. Any clinically significant ECG abnormalities at baseline should be documented in the baseline signs and symptoms section in the CRF. Additional clinically significant ECG abnormalities occurring during the study should be documented on the adverse event forms. ECGs will be reviewed by a core laboratory at the end of the study.

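### The ECG safety objective is analysed only by judgement-based categories; PR, QRS and QTc change from baseline is not summarised as a number

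*Protocol*

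**What the plan says.** Section 2.2 of the protocol sets out to investigate safety and tolerability "through observations of adverse experiences, vital signs, laboratory tests, and effects on 12-lead ECG".

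Section 6.2.2 gives the data: "A standard 12-lead ECG will be recorded at Visits 2 (or at visit 1 if it is logistically easier) and 5". The Visit 5 trace may be taken up to 24 hours before surgery. The same section adds that "ECGs will be reviewed by a core laboratory at the end of the study", without saying what that review measures.

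Section 11.8.4.2 is the whole ECG analysis. "The results from these will be classified as normal, abnormal not clinically significant and abnormal clinically significant". Results at Visits 2 and 5 "will also be classified as no clinically significant change from baseline or clinically significant change from baseline". Both classifications are summarised by treatment group, and clinically significant findings are listed and summarised. No ECG interval is named anywhere in the protocol.

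The neighbouring safety sections differ. For vital signs (11.8.4.1), "Absolute change from baseline will also be calculated for each subject and summarised by visit and treatment group". For laboratory tests (11.8.3), "Laboratory data will be summarised for each parameter at all visits by treatment group", again with absolute change from baseline, and threshold categories are reported as well.

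**The concern.** A paired trace, baseline and on treatment, is planned for every patient, and a core laboratory reviews all of them. The plan then keeps only a rating and a yes/no judgement. Laboratory data get both numbers and categories and vital signs get numbers, but the ECG gets categories alone, and no reason is given.

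This affects what the objective can deliver. A category changes only when a reader judges the trace to have crossed a line. A modest average lengthening of an interval can leave most patients in the category where they started. That is likelier in this population: section 5.2.2 excludes myocardial infarction only within the previous 4 weeks, and unstable angina, so patients with abnormal baseline traces may enter. The human exposure reported in section 1.1 is in healthy subjects, so a placebo-controlled comparison in patients with carotid disease is worth using fully. As written, the plan gives no estimate of interval change in any arm.

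**Working it through.** **The plan's own figures.** The protocol states no ECG sample size, variability, power or precision, so there is no ECG figure to reproduce. The group size comes from the primary endpoint (section 11.4.1): difference 0.693, SD 0.7 on the log scale, two-sided 2.5%. With 27 per group the noncentrality is 0.693 / (0.7 × √(2/27)) = 3.64 on 52 degrees of freedom, giving 90.5% power, in line with the stated 90%. The protocol randomises 33 per group, and that number is used below.

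**Assumptions for the illustration (none is in the protocol).** Change in QTc is normal, with SD 15, 20 or 25 ms and mean zero on placebo. The true mean shift on one dose is 5 to 20 ms. Tests are two-sided at 5%. Because the protocol gives no numerical meaning for a clinically significant change, a rise above 30 ms or above 60 ms stands in for it.

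**Mean change.** SE = SD × √(2/33) = 3.69, 4.92 and 6.15 ms. For a 10 ms shift the noncentrality 10/SE is 2.71, 2.03 and 1.62 on 64 degrees of freedom, giving power of 76%, 52% and 36%. The 95% CI half-width is 1.998 × SE = 7.4, 9.8 and 12.3 ms.

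**Yes/no rule at more than 30 ms.** The proportion above the line is 1 − Φ(30/SD) on placebo and 1 − Φ((30 − shift)/SD) on the dose. For a 10 ms shift this gives 2.3% against 9.1%, 6.7% against 15.9%, and 11.5% against 21.2%. Exact power of Fisher's test is 4%, 10% and 11%.

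Ranges over SD 15-25 ms, 33 per arm:

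| True shift | Mean change | Rule >30 ms | Rule >60 ms |
|---|---|---|---|
| 5 ms | 13-27% | 0.2-3% | <1% |
| 10 ms | 36-76% | 4-11% | <1% |
| 15 ms | 67-98% | 26-32% | <1% |
| 20 ms | 89-100% | 50-70% | <1% |

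At 10 ms the gap is 25 to 72 percentage points, depending on the SD (36.0 − 10.7 and 76.0 − 3.8). Fewer than 33 per arm may have a Visit 5 trace; with 27, the 10 ms figures are 30-67% against 2-7% for the 30 ms rule.

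**If no events are seen.** Zero events among 33 patients gives a one-sided 95% upper limit for the event rate of 1 − 0.05^(1/33) = 8.7%. It says nothing about the mean interval.

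**The case against.** The strongest reply is that interval tables are ordinary analysis-plan detail, and the Reporting and Analysis Plan is not at hand. It could add them, so it is not shown that intervals will never be analysed. But section 11.8.3 expressly leaves its laboratory thresholds to that plan, whereas 11.8.4.2 defers nothing and fixes the scale. The point is about a choice the protocol makes.

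Second, the power comparison uses a rule that the protocol does not contain. Section 10.4 leaves the clinical significance of an abnormal assessment to the investigator's judgement, and 6.2.2 uses the same term for ECG abnormalities. It is not stated to be a cut of QTc. This stands: the calculation only illustrates how much a yes/no reading can lose.

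Third, no ECG test is planned, and the laboratory and vital-sign summaries carry no placebo contrast or confidence interval either. This also stands. Summarising change from baseline brings the ECG level with the protocol's own practice; the difference from placebo with its interval goes a step further.

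Fourth, a reader might infer that any drug effect on the ECG would be almost undetectable, with near-zero counts in each arm regardless. The figures do not support that. At 15-20 ms the 30 ms rule reaches 26-70%. Even at 10 ms with SD 20 ms the expected counts are about 2 and 5 of 33 (33 × 6.7% and 33 × 15.9%). Nor is heart rate neglected: it is measured with the vital signs (6.2.1), scheduled at Visits 2 and 5 in Appendix 1, and summarised as change from baseline under 11.8.4.1.

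Finally, the trial is small. With one trace per visit, even mean change has only 13-27% power for a 5 ms shift.

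**Conclusion.** The point holds as a low-cost improvement to a secondary safety analysis; the primary endpoint is untouched. Section 11.8.4.2 analyses a stated objective by category only and drops the numerical change that the adjacent sections keep. Under the assumptions above, mean change has higher power than the 30 ms and 60 ms rules at every shift and SD examined, and would give a 95% CI half-width of about 7-12 ms for each dose against placebo. The loss is largest in relative terms for shifts up to about 10 ms. For larger shifts it depends on where the undefined line falls: substantial detection at 30 ms, below 1% at 60 ms. The SDs, shifts and thresholds are all assumed, and the protocol claims no ECG power, so the numbers measure information given up and do not show that a stated property fails.

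**What to change.** Add to section 11.8.4.2: *PR, QRS and QTc read by the core laboratory from the Visit 2 (or Visit 1) and Visit 5 traces will be summarised by treatment group as values and as change from baseline. The difference of each dose from placebo in mean change, adjusted for the baseline value, will be given with its 95% confidence interval.* Keep the categorical tables and the listing. Heart rate needs no addition.

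No new visit, procedure or patient is needed, since the traces are already taken and centrally reviewed. The cost is one extra table and the reporting of interval values. Whether the core laboratory supplies those values must be confirmed, because section 6.2.2 does not say what it measures.
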